# Protocol of an expertise based randomized trial comparing surgical Venae Sectio versus radiological Puncture of Vena Subclavia for insertion of Totally Implantable Access Port in oncological patients

**DOI:** 10.1186/1745-6215-9-60

**Published:** 2008-10-24

## Abstract

**Background:**

Totally Implantable Access Ports (TIAP) are being extensively used world-wide and can be expected to gain further importance with the introduction of new neoadjuvant and adjuvant treatments in oncology. Two different techniques for the implantation can be selected: A direct puncture of a central vein and the utilization of a Seldinger device or the surgical Venae sectio. It is still unclear which technique has the optimal benefit/risk ratio for the patient.

**Design:**

A single-center, expertise based randomized, controlled superiority trial to compare two different TIAP implantation techniques. 100 patients will be included and randomized pre-operatively. All patients aged 18 years or older scheduled for primary elective implantation of a TIAP under local anesthesia who signed the informed consent will be included. The primary endpoint is the primary success rate of the randomized technique. Control Intervention: Venae Sectio will be employed to insert a TIAP by a surgeon; Experimental intervention: Punction of V. Subclavia will be used to place a TIAP by a radiologist. Duration of study: Approximately 10 months, follow up time: 90 days.

**Organisation/Responsibility:**

The PORTAS 2 – Trial will be conducted in accordance with the protocol and in compliance with the moral, ethical, and scientific principles governing clinical research as set out in the Declaration of Helsinki (1989) and Good Clinical Practice (GCP). The Center of Clinical Trials at the Department of Surgery, University Hospital Heidelberg is responsible for design and conduct of the trial including randomization and documentation of patients' data. Data management and statistical analysis will be performed by the independent Institute for Medical Biometry and Informatics (IMBI), University of Heidelberg.

**Trial Registration:**

The trial is registered at ClinicalTrials.gov (NCT00600444).

## Background

The first implantation of a TIAP was performed and described by Niederhuber et al. in 1982. Since then the insertion of a TIAP is a routinely employed technique in patients who need a safe and permanent venous access for chemotherapy, parenteral nutrition, recurrent blood sampling or other reasons [1]. This system needs no external dressing, allows the patient normal physical activity, is probably less prone to infectious complications and will minimize the occlusion rate of the catheter compared to non-totally implantable catheters [1]. TIAPs are being extensively used world-wide and an increase in the number of port placements can be expected. In Germany 70233 TIAP inpatient implantations were performed in 2006 (Federal Statistical Office, Wiesbaden, Germany). The number of TIAP implantations increased constantly at our Department from 169 in 1997 to 754 in 2007.

Today two different approaches to implant a TIAP are usually employed. Venae Sectio (VS) of the cephalic vein performed predominantly by surgeons and Puncture of Vena Subclavia (PVS) performed by interventional radiologists or surgeons. While most common complications can be observed with both techniques such as "pinch off" phenomena, kinking or dislocation of the catheter, subcutaneous hematoma, nerve palsy and wound infection, there are specific risks only associated with PVS like pneumo- and haematothorax [1,2].

Correct placement of the TIAP in the superior Vena Cava is mandatory for optimal and safe function of the central venous access. The median success rate of TIAP implantation via the conventional approach by transsection of the cephalic vein is 80% in various prospective and retrospective trials [2]. In contrast PVS achieved a success rate between 98 to 100%, up to now in retrospective studies [3-8].

## Study design

### Aim of study

The comparison of VS performed by a surgeon versus PVS performed by an interventional radiologist.

### Number of patients needed

A review of published literature showed a median primary success rate of 80% for the VS in retro- and prospective studies [1,2,9-15]. PVS achieved a median primary success rate of 99% in various retrospective studies [3-8]. The group size for double sided testing was calculated with Simple Interactive Statistical Analysis (SISA) [16]. If the difference in success rate is 19% (80% vs. 99%) there will be an 80% chance that a trial involving 100 patients (50 per group) could detect a significant difference at an alpha level of 5% (Figure 1). We decided to calculate the sample size on the results of previous studies instead of calculating the sample size on a defined minimal clinical important difference because all mentioned previous studies showed a consistent median difference of 19%. This offers the opportunity to test these results the first time in a RCT setting with an economical sample size.

**Figure 1 F1:**
[figure not shown]
Flowchart according to CONSORT.

### Eligibility

#### Inclusion criteria

• Benign and malignant diseases which demand a safe and permanent venous access, e.g. for chemotherapy or parenteral nutrition

• Age 18 years or older

• Patients scheduled for primary elective implantation of TIAP under local anesthesia

• Informed consent

#### Exclusion criteria

• Participation in another intervention-trial with interference of intervention and outcome of this study

• Lack of compliance (assessed by the trial investigator)

• Impaired mental state or language problems (Patient is not able to read German)

• Patients with known allergy to contrast agent

#### Subject withdrawal criteria

• At their own request or at request of the legal representative

• If, in the investigator's opinion, continuation of the trial would be detrimental to the subject's well-being

All withdrawn patients will be reported in the final results to guarantee maximum transparency.

### Consent

Patients who are assigned for port-catheter-system implantation either at the Department of Radiology or Surgery, University hospital of Heidelberg, will be screened for their eligibility and informed about the PORTAS 2 trial during a visit prior to treatment. The study procedure, risks, benefits and data management will be clarified in detail before the patients are asked to give their informed consent. After inclusion of the patient his personal data (height (cm), weight (kg), gender, smoking customs, Karnowsky-Index (0 – 100%), medication of immunsuppresion, antibiotics (yes/no), chemotherapy (yes/no)) will be recorded into the CRF (Table 1).

**Table 1 T1:** Study visit schedule

			Follow-up
			
	Day of screening	Day of operation	Visit 1 (day 90 post OP) by phone
Past medical history*	X		

Informed consent	X		

Personal data**	X		

Examination of primary endpoints:			
• Success of randomized implantation technique		X	

Examination of secondary endpoints:			
• Peri- and postoperative complications		X	X
• Times of port implantation procedure		X	
• Dose of radiation		X	

Savety criteria AE, SAE (2.6)		X	X

* study-relevant past medical history, past surgical history

** height (cm), weight (kg), gender, smoking customs, Karnowsky-Index, medication of immunsuppresion, antibiotics, chemotherapy

### Randomization and procedures for minimizing bias

#### Minimizing bias

To achieve comparable groups for known and unknown risk factors randomization will be performed as unstratified block randomization with random block sizes in a 1:1 allocation ratio. Allocation to treatment group will be carried out by the randomization software RITA^®^[17]. 110 patients will be recruited according to the sample size calculation. Randomization will be performed by a study nurse of the Clinical Study Center Surgery (KSC) expertise based to the Department of Surgery for patients in group A and to the Department of Radiology for patients in group B. Randomization will be carried out after patient signed the informed consent. Intervention will be scheduled 1–4 days after inclusion depending on the earliest operation appointment possible.

#### Minimizing treatment bias

All physicians who participate in this trial will be trained and updated every 3 months to guarantee comparable treatment of patients. Special manuals will be used in the operation and the radiology room to reduce error. The same TIAP device will be implanted in all patients (INTRAPORT II Keramic^® ^by Fresenius Kabi). Antibiotic prophylaxis will only be given to patients with risk for endocarditis according to the local standards or to patients scheduled for a chemotherapy < 5 days after implantation.

#### Minimizing measurement bias

A study nurse will document and monitor the procedure in the operating theatre or radiological intervention room. Blinding is not possible due to the nature of surgery and the allocation to different departments.

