##### Postoperative complications

• thrombosis

• postoperative bleeding

• hematoma

• disconnection or breakage of the catheter

• extravasation of injected fluid

• wound infection

• cutaneous necrosis

Definitions are shown in Table 2 and Table 3

**Table 2 T2:** Definitions of perioperative complications.

Pneumothorax	Radiological findings
Hematothorax	Radiological findings or sonografic findings

Intraoperative lesion of nerves	Clinical diagnosis or EMG findings

Dislocation of the catheter or the port chamber	Radiological finding

Intolerance of contrast agent	Any allergic reaction of contrast agent which requires any application of drugs

**Table 3 T3:** Definitions of postoperative complications.

Thrombosis	Sonographic findings or phlebography
Postoperative bleeding	Clinical diagnosis during reoperation

Hematoma	Clinical diagnosis, no reoperation necessary

Disconnection or breakage of the catheter	Radiological findigs, findings after explantation

Extravasation of injected fluid	Radiological findings or clinical diagnosis

Wound infection	Clinical diagnosis. Reopening of wound necessary or antibiotic treatment.

Catheter sepsis	Two or more of the following symptoms:
	• temperature over 38.3°C or under 36°C
	• heart frequency over 90 beats per minute
	• breath frequency over 20 breaths per minut, PaCO2 < 32 mmHg (spontan breathing) or PaO2/FiO2 < 200 mmHg (mechanical ventilation)
	• Total peripheral WBC count > 12 G/L or WBC < 4.0 G/L or > 10% immature neutrophils (bands), regardless of total peripheral WBC count
	• Plasma C-reactive protein > 2 SD above normal value

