##### Assessment

1. Perioperative complications of port implantation will be recorded with tick boxes at day of operation by an independent study nurse.

2. Postoperative complications of port implantation will be recorded with tick boxes at day of operation and visit 1 (90 days after operation) after a standardized telephone interview by a study nurse. A confirmation by the responsible family physician will be requested by any abnormality reported by the patient.

The duration of port implantation procedure

• Time from first skin incision to last knot of intracutaneous suture

• Time from patient entering until patient leaving intervention room

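### The blanket statement that blinding is impossible does not cover the nurse who makes the day-90 telephone interview, who could be kept largely unaware of allocation

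*Protocol article*

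**What the plan says.** The protocol article's only statement on blinding is under Minimizing measurement bias: "Blinding is not possible due to the nature of surgery and the allocation to different departments". It follows a sentence about the day of the procedure: "A study nurse will document and monitor the procedure in the operating theatre or radiological intervention room".

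The study visit schedule (Table 1, under Consent) has one follow-up contact, headed "Visit 1 (day 90 post OP) by phone". According to the Assessment text under Secondary endpoints, postoperative complications are ticked off on the day of operation and again at day 90, the latter "after a standardized telephone interview by a study nurse". The confirmation rule follows: "A confirmation by the responsible family physician will be requested by any abnormality reported by the patient".

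For perioperative complications the same section describes the assessor differently: "Perioperative complications of port implantation will be recorded with tick boxes at day of operation by an independent study nurse". The day-90 caller is not described as independent or as masked.

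**The concern.** The two reasons given for not blinding are the nature of surgery and the use of two departments. Both concern people who see the procedure, perform it or undergo it. A nurse who telephones 90 days later, and need not see the patient, the wound or the room, is not covered by either. The statement is therefore broader than its own justification. It sits in the section on measurement bias, and it rules out a protection that the follow-up procedure would allow.

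What is at stake is the comparison of postoperative complications. This is a named secondary endpoint and the risk side of the benefit/risk question in the Abstract. If the caller knows the arm, follow-up questions and the handling of vague answers may differ between arms. An event that does not come out in the call does not reach the family physician.

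**Working it through.** The protocol gives no figure on this point to reproduce, so the check sets its statements side by side.

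**1. Whom do the stated reasons cover?**

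| Role | Necessarily knows the arm? | Why |
|---|---|---|
| Operator | Yes | Performs the technique |
| Patient | Yes | Is treated in one of two departments, with visibly different steps (Study treatment) |
| Study nurse in the room | Yes | Documents and monitors the procedure (Minimizing measurement bias) |
| Study nurse who randomizes | Yes | Directs the patient to one department (Minimizing bias) |
| Study nurse who calls at day 90 | No | Contact is by telephone only (Table 1; Assessment) |

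Only the last row falls outside the stated reasons.

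**2. How does a later complication enter the data?** Table 1 schedules complication and safety recording on the day of operation and at day 90 only. For an event arising in between, the planned route is: the patient reports it in the call, the nurse ticks the box, and the family physician is asked to confirm. The last step depends on the first. Confirmation can remove a false positive, but as written it cannot recover an event that was never mentioned. Unscheduled contact may bring some events to light, but the article does not rely on it.

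**3. Which events are exposed?** From Table 3:
- Hematoma rests on clinical diagnosis without reoperation. This is the most exposed.
- Extravasation and cutaneous necrosis may be diagnosed clinically, or by radiology and histology respectively. These are partly exposed.
- Wound infection is defined as "Clinical diagnosis. Reopening of wound necessary or antibiotic treatment". The need for reopening or treatment anchors it, so it is less exposed.
- Thrombosis (sonography or phlebography), postoperative bleeding (reoperation), disconnection or breakage (radiology or explantation) and catheter sepsis (clinical criteria plus bacteriology) rest on findings that a caller cannot create. They could be missed if not elicited, but are least open to the caller's influence.

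**4. Can the size be computed?** With n patients per arm, a true rate p_A or p_B, and a proportion s_A or s_B of true events picked up, the expected recorded counts are n·p_A·s_A and n·p_B·s_B. If the true rates are equal, the apparent ratio is s_A/s_B. The sample size section gives a planned n of 50 per group. The article gives no complication rate and no pick-up proportion for either arm, so neither the ratio nor its direction can be derived.

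**5. Is the primary endpoint touched?** No. Primary success is judged around the procedure by the responsible physician, confirmed by a study nurse and compared with the operation report, and a radiograph is stored (Assessment of the primary endpoint). The day-90 call plays no part in it, and the sample size rests on the primary endpoint alone.

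**The case against.** The case against has several good points.

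- **The trigger belongs to the patient.** A reader might infer that the caller decides what counts as an abnormality. The text does not say so: any abnormality that the patient reports leads to a request. What survives is narrower, namely that the caller can influence what the patient is led to report.
- **Safeguards exist.** The interview is standardized, the physician is asked to confirm, and the surgical and radiological coordinators both cross-check SAEs and AEs (Adverse events and serious adverse events). Data management and analysis lie with an independent institute. These count. However, confirmation and cross-check are described for events already reported, and standard questions do not fix how a vague answer is followed up.
- **The call may not be the main source.** A reader might infer that it yields most postoperative complications. The documents give no split, and these complications are also recorded on the day of operation. It can only be said that the call is the sole scheduled contact after that day.
- **Who calls is not stated.** It would be speculation that the caller is the nurse who watched or randomized the patient. The text does not exclude it, and an article may leave rotas to the full protocol. The point therefore rests on the over-broad sentence that is stated, not on the missing rota.
- **The setting proves nothing.** The trial is run from the surgical department that supplies one arm. A reader might infer a bias towards that arm, but nothing in the documents shows one.
- **Masking would be imperfect.** Patients know their arm, may reveal it, and may report differently because of it. A masked caller does not cure that. This limits the benefit but does not cancel it.

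**Conclusion.** The point holds as a minor one. The protocol states without limit that blinding is not possible, while its reasons stop short of the day-90 telephone interviewer. An unmasked caller could cause differential ascertainment of postoperative complications, chiefly clinically diagnosed ones such as hematoma, and less so those that need imaging, reoperation, bacteriology or treatment. The existing safeguards reduce the risk without removing it.

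The size and direction of any bias cannot be computed from the documents, and any numerical ratio would rest on invented rates. The primary endpoint, its analysis and the sample size are unaffected. The conclusion assumes that the call needs no knowledge of the allocation, which fits a standardized tick-box interview, and that follow-up questioning leaves the caller some latitude, which is an inference.

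**What to change.** Limit the sentence under Minimizing measurement bias to operators, patients and procedure-room staff. In the Assessment text for postoperative complications, state that:

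- the day-90 call is made by an existing study nurse who neither attended the procedure nor randomized that patient;
- the call sheet shows neither allocation nor department;
- the request to the family physician is worded neutrally as to allocation;
- the nurse records whether the allocation became known during the call.

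The cost is rota planning and the rewording of two forms, using study nurses already in the trial. Sample size, endpoints and primary analysis do not change. The masking will be partial because some patients will reveal their arm. The unmasking record lets the report say how often that happened.

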### Study treatment

All patients will be positioned on the table in a five degree reverse Trendelenburg's position. The neck, chest and shoulders of the patients will be prepared and draped in the customary sterile manner.

The left V. Subclavia/V. Cephalica will be preferred except for one of the following cases:

• patient suffers from breast cancer on the left side

• patient is left-handed

• prior evidence that left V. subclavia is closed by a thrombosis

• patient's wish

• patient had port catheter on left side before

According to the allocation the procedure will be continued:

#### Intervention-group A (Venae Sectio performed by a surgeon)

Local anesthesia will be infiltrated in sterile fashion into skin and subcutaneous layer and skin incision will be performed 4 cm inferolaterally over the deltoideo-pectoral sulcus region. The cephalic vein is to be exposed. The cephalic vein will be ligated distally and encircled cranially with a reabsorbable suture. The vein will be cross-sected ventrally and the catheter flushed with heparinized saline, then introduced (figure 2, 3). The introduction of the catheter may be supported by use of a guiding wire, vein dilatator and peel away sheath if necessary. After placement of the catheter the correct positioning will be controlled via fluoroscopy (tip of catheter in the V. cava superior just to the tune of the bronchial bifurcation). The catheter will be connected to the port chamber. Using the same incision, a subcutaneous pocket will be prepared on the pectoral fascia. The port chamber will be fixed on the fascia of the pectoral muscle with three single non absorbable sutures. The wound will be closed with an absorbable subcutaneous suture and skin will be closed by a non absorbable intracutaneous suture. Unhindered flow for blood withdrawal and infusion is verified by cutaneous puncture (Huber needle). To complete the procedure the system is blocked with 2–4 ml heparinized saline (100 I.E./ml).

**Figure 2 F2:**
[figure not shown]
Venae Sectio – incision of cephalic vein.

**Figure 3 F3:**
[figure not shown]
Venae Sectio – introducing of TIAP catheter.

#### Intervention-group B (Punction of V. Subclavia by a radiologist)

Patients receive a peripheral venous catheter on the side of planned puncture location for the administration of contrast agent (Ultravist^® ^370 by Bayer) and the verification that the V. subclavia is not closed by thrombosis (road-map technique, figure 4). Local anesthesia will be introduced in sterile fashion into skin and periost of the clavicula. Location of the puncture will be marked between proximal and medial third of the clavicula (figure 5). A ca. 2 cm wide skin incision will be performed above puncture location. In the following the V. Subclavia is punctured under fluorscopy using the Seldinger technique and a guiding wire is introduced (figure 6, 7). An introducer sheath is passed via the guiding wire into the V. subclavia. The guiding wire is removed and the port catheter may be introduced through the introducer sheath. Correct position is verified by fluoroscopy. A second ca. 3,5 cm wide skin incision is performed 1 cm below the first incision parallel to the clavicula. A subcutaneous pocket will be prepared on the pectoral fascia. The port chamber will be fixed on the fascia of the pectoral muscle with three single non absorbable sutures. The wound will be closed with an absorbable subcutaneous suture and skin will be closed by a non absorbable intracutaneous suture. Correct position of port catheter is checked again by fluorscopy (Tip of catheter in the V. cava superior just to the tune of the bronchial bifurcation). Flow for blood withdrawal and infusion is tested via cutaneous puncture (Huber needle). To complete the procedure the system is blocked with 2–4 ml heparinized saline (100 I.E./ml).

**Figure 4 F4:**
[figure not shown]
Puncture of V. Subclavia – demonstration of V. Subclavia with contrast agent.

**Figure 5 F5:**
[figure not shown]
Puncture of V. Subclavia – puncture.

